## Abstract

**Background:**

Many people with diabetes have suboptimal glycaemic control due to not being adherent to their treatment regimen. Behavioural economic theory suggests that the lack of adherence results from the disconnect between the timing of when costs and benefits accrue. One strategy to address this discontinuity is to offer patients a near-term benefit, such as a financial reward. Whereas there is evidence that rewards can improve treatment adherence and sometimes health outcomes, further research is needed to determine whether rewards are more effective when targeting processes or intermediary health outcomes. In the Trial to Incentivise Adherence for Diabetes (TRIAD) we test whether adding financial incentives to usual care can improve HbA1c levels among people with diabetes and whether the financial incentives work better when targeting processes (adherence to blood glucose testing, medication, and daily physical activity) or the primary intermediary health outcome of self-monitored blood glucose within an acceptable range.

**Methods/design:**

TRIAD is a randomised, controlled, open-label, single-centre superiority trial with three parallel arms. A total of 240 patients with suboptimally controlled diabetes (HbA1c ≥ 8%) from a polyclinic in Singapore are block-randomised (blocking factor: current vs. new glucometer users) into three arms, namely (1) usual care (UC) only, (2) UC with process incentive and (3) UC with outcome incentive, in a 2:3:3 ratio. Masking the arm allocation will be precluded by the behavioural nature of the intervention but blocking size will not be disclosed to protect concealment. The primary outcome (change in HbA1c level at month 6) will be measured by a laboratory that is independent from the study team. Secondary outcomes (at month 6) include the number of blood glucose testing days, glucose readings within the normal range (between 4 to 7 mmol/L), medication-adherent days, physically active days, and average incentives earned and time spent administrating the incentives.

**Discussion:**

This study will provide evidence on whether financial incentives can cost-effectively improve glycaemic control. It will also provide evidence on the benefit incidence of interventions involving financial incentives. By comparing process to outcome incentives, this study will inform the design of future incentive strategies in chronic disease management and beyond.

**Trial registration:**

ClinicalTrials.gov registry, ID: NCT02224417. Registered on 22 August 2014.

**Electronic supplementary material:**

The online version of this article (doi:10.1186/s13063-017-2288-6) contains supplementary material, which is available to authorized users.

## Background

### Rationale

In 2014, there were 422 million adults with diabetes worldwide [1]. Diabetes is associated with a host of adverse complications, including myocardial infarction, stroke, blindness, kidney failure and severe neuropathy that may result in amputations [2]. The global direct healthcare cost of diabetes and its complications was estimated to exceed USD827 billion in 2014 [3, 4]. In Singapore, diabetes is the cause of 10.4% of all disability-adjusted life years (DALYs) lost, which represents the fourth most important disease burden [5].

Diabetes management primarily consists of promoting glycaemic control via diet, physical activity; and, if necessary, medication. Medication generally includes oral hypoglycaemic agents, which may be followed by injectable insulin when blood glucose remains suboptimally controlled. In 2012, higher-than-optimal blood glucose was responsible for 2.2 million of the 3.7 million deaths caused by diabetes worldwide [2]. In 2010 in Singapore, about a third (32%) of known people with diabetes had suboptimal glycaemic control as defined by a concentration of glycated haemoglobin (HbA1c) of 8.0% or more [6].

While treatment effectiveness crucially depends on the quality of care provided by health professionals (e.g. efficacious medications, clear and appropriate advice, relevant health education and support), patient engagement is especially important to chronic disease management as most of the treatment takes place outside the healthcare system. In 2003, the World Health Organisation reported that, worldwide, only 50% of patients suffering from chronic diseases were adherent to their treatment. Regarding diabetes, all aspects of treatment (glucose monitoring, administration of medication, diet and physical activity) were affected by non-adherence. As a result, much research was conducted in efforts to improve diabetes management. Meta-evidence on the average reduction in HbA1c levels achieved by various types of interventions shows that education on diabetes self-management reduces HbA1c levels by 0.57 percentage points [7], self-monitoring of glucose levels reduces these levels by 0.25 percentage points [8], behavioural interventions targeting physical activity reduces HbA1c levels by 0.32 percentage points [9], and computer-based interventions to improve diabetes self-management reduces HbA1c levels by 0.20 percentage points [10]. In their review of quality improvement strategies on the management of diabetes, Tricco and colleagues found an average reduction in HbA1c levels of 0.37 percentage points and note that strategies targeting patients were on average more effective [11]. While all were statistically significant, the above meta-estimates reveal modest-to-moderate effect sizes. Improvement in glycaemic control in the population remains extremely slow [12], and more generally, the rise in number of people with multiple comorbidities makes treatment adherence even more difficult to achieve overall.

Behavioural economic theory may provide an explanation for the lack of adherence to treatment recommendations: the benefits of greater efforts of adherence only arise well into the future whereas the costs are immediate. When costs and benefits are so far apart, individuals have been shown to be biased towards the present, which results in decisions that are time-inconsistent and that generate significant regret [13]. One strategy that addresses such present bias is to provide patients with near-term benefits. This can be achieved by providing patients with financial incentives that are contingent on treatment adherence. Recent research on financial incentives uses behavioural economics in efforts to generate the largest behavioural change. For instance, studies are leveraging patients’ loss aversion with deposit contract incentives [14] and adherence contingent rebates [15], and patients’ probabilistic assessment bias with lottery incentives [14, 16, 17].

Evidence on the effectiveness of financial incentives for diabetes management is scarce. Long and colleagues found a reduction in HbA1c level of 0.45 percentage points among African American Veterans with diabetes by tying rewards to HbA1c reductions but this effect was not statistically significant [18]. Sen and colleagues found that a lottery incentive tied to glucose monitoring improved monitoring rates by 19 to 23 percentage points among uncontrolled people with diabetes in a US primary-care medical home practice [19].

The first primary objective of this trial is to determine whether adding financial incentives to usual care (UC) can improve HbA1c levels among people with suboptimally controlled type-2 diabetes in the primary-care setting. The second primary objective is to determine whether financial incentives should be directed at processes (adherence to blood glucose testing, medication, and daily physical activity) or at achieving intermediary health outcomes (self-monitored blood glucose within acceptable range). This trial will provide novel head-to-head evidence on which strategy works best. In addition, the trial will assess the effect of financial incentives on treatment adherence and whether such incentives constitute cost-effective intervention strategies for diabetes management. Finally, explanatory analysis will aim at determining whether patient perception about diabetes management is altered by the interventions, uncovering factors that might moderate the effect of financial incentives, and identifying socioeconomic groups that may benefit more from the interventions.

### Objectives

#### Primary objective 1

To determine whether complementing UC with financial incentives for good treatment adherence is superior to UC alone in reducing HbA1c at 6 months.

#### Primary objective 2

To determine whether incentivising intermediate health outcomes (self-monitored blood glucose levels within acceptable range) is superior to incentivising intermediate processes (blood glucose testing, physical activity, and medication adherence) in reducing HbA1c at 6 months.

#### Secondary objective 1

To assess whether complementing UC with financial incentives for good treatment adherence is superior to UC alone in improving treatment adherence as measured by the proportion of glucose tests and medications taken as prescribed and average number of daily steps taken between baseline and 6 months.

#### Secondary objective 2

To assess whether incentivising health outcomes is superior to incentivising intermediate processes in improving treatment adherence as measured by the proportion of glucose tests and medications taken as prescribed and average number of daily steps between taken baseline and 6 months.

#### Secondary objective 3

To assess which intervention (i.e. incentivising health outcomes or processes) has the most favourable incremental cost-effectiveness ratio (ICER) for HbA1c reductions between baseline and 6 months compared to UC alone.

## Methods/design

### Trial design

The Trial to Incentivise Adherence for Diabetes (TRIAD) is designed as a randomised, controlled, single-centre superiority trial with three parallel arms. A total of 240 people with suboptimally controlled diabetes will be block-randomised (blocking factor: current vs. new glucometer users) into the usual care (UC), process incentive and outcome incentive arms in a 2:3:3 ratio. The study intervention will last for 6 months. The primary outcome is change in HbA1c level as measured by blood tests at baseline and month 6. This protocol conforms to the Standard Protocol Items: Recommendations for Interventional Trials (SPIRIT) guidelines. (Additional file 1: SPIRIT Checklist and Fig. 1: SPIRIT Figure).

**Fig. 1 Fig1:**
[figure not shown]
Standard Protocol Items: Recommendations for Interventional Trials (SPIRIT) Figure. *HbA1c* glycated haemoglobin, *EQ-5D-5L* European Quality of Life-5 Dimensions-5 Levels, *BIPQ* Brief Illness Perception Questionnaire, *SMBG* self-monitoring of blood glucose, *BMQ* Beliefs about Medication Questionnaire, *DSCA* Diabetes Self-Care Activities

### Study setting and eligibility criteria

All the participants with suboptimally controlled diabetes will be recruited among the patients from the SingHealth Polyclinic in Geylang, Singapore. Singapore is a densely populated island city-state that has a population of 5.5 million. It is made up of Chinese (76.2%), Malay (15%), Indian (7.4%) and other (1.4%) ethnicities. It is a multi-cultural country with the most widely spoken languages being English, Mandarin, Malay and Tamil. A large proportion of those who speak Malay and Tamil are also proficient in English.

SingHealth Polyclinics are part of SingHealth, which is Singapore’s largest public healthcare group. SingHealth has a network of nine Polyclinics in Singapore, providing primary healthcare to local communities that is designed to be affordable and accessible to all. Services provided at the polyclinics include medical care for acute and chronic conditions, medical examinations and screening, minor surgical procedures and clinical laboratory services. SingHealth Polyclinics has a research department with three signature research programmes, including Chronic Disease Management, Education Research and Innovation in Primary Care. The study will be conducted in collaboration with Duke-NUS Medical School as part of the SingHealth Duke-NUS Academic Medical Centre.

#### Inclusion criteria

Have suboptimally controlled diabetes at baseline. Suboptimally controlled diabetes is defined by a HbA1c level of 8.0% or greater. As such, patients will be required to have at least one of two HbA1c readings of 8.0% or greater in the past 6 monthsBe prescribed at least one oral diabetic medication for at least 3 monthsAged between 21 and 70 years of ageBe Singaporean citizens or permanent residentsBe able to converse in English or Mandarin

#### Exclusion criteria

Patients taking injectable insulin therapyPatients with significant comorbid conditions such that they are unlikely to be able to take their medications without assistance from a third partyPatients who are pregnantPatients who answer ‘yes’ to at least one question of the Physical Condition Questionnaire, or indicate having a heart condition or disease, a stroke, or a lung disease (chronic obstructive pulmonary disease or asthma), or report that an immediate family member (mother, father, sister or brother) had a myocardial infarction or died of a heart-related disorder before age 55 (men) or 65 (women) years will be excluded from the study unless they receive approval from a physician who is not part of the study team

### Participant timeline and study arms

Participants in all three study arms will be issued with one Fitbit Zip™ and one eCAP™. A Fitbit Zip™ (Fitbit Inc., San Francisco, CA, USA) is a pedometer with wireless synchronisation to smartphones and computers. It tracks daily steps taken, calories burned and distance walked. An eCAP™ (Information Mediary Corporation, Ottawa, ON, Canada) is a medication-event monitoring system with an inbuilt electronic tag which records the time whenever it is closed. Participants will also use a glucometer for the study. A glucometer is a medical device that measures blood glucose levels. It is estimated that approximately half of the study participants will already use a glucometer before joining the study. Participants without a glucometer will be provided with a Nipro TRUEresult™ glucometer which they may keep after the study ends. The project coordinator will label the study devices with the participant’s unique ID number as allocated at randomisation. The clinical research coordinator (CRC) will demonstrate how to adequately use all study devices. Participants who have difficulties with their glucometer will be referred to a health counsellor at the polyclinic. Participants in all study arms will attend baseline, month 3 and month 6 assessments. At the baseline and month-6 assessments, the participants will fill out survey questionnaires (see the ‘Data collection’ section below) and take HbA1c blood tests. At the month-3 and month-6 assessments, the CRC will use the data from the three study devices to evaluate treatment adherence and the corresponding incentive payments in supermarket vouchers when applicable. At the month-18 assessment, a month-18 checklist based on participants’ medical records will be filled up by the CRC. Participants’ HbA1c blood test result since their month-6 assessment and any change in diabetes medication regimen (e.g. initiation of insulin) will be recorded. Figure 2 displays the timeline of the participants in the study.

**Fig. 2 Fig2:**
[figure not shown]
Trial to Incentivise Adherence for Diabetes (TRIAD) participant timeline

Participants in the UC arm will not receive any financial incentives for meeting the recommended goals, but they will receive a non-contingent payment at the end of the intervention. Participants in the process incentive arm will have the opportunity to earn financial incentives for meeting specified goals for physical activity, medication adherence and blood glucose testing. The participants in the outcome incentive arm will have the opportunity to earn financial incentives for meeting specified goals for blood glucose testing. In addition, participants in all study arms will be compensated to attend the assessment visits. Table 1 summarises the incentive scheme that applies to each study arm.

**Table 1 Tab1:** Financial incentives per study arm

Study arm	Contingent incentives	Non-contingent payment	Assessment incentives	Total payments
Control	None	Yes (SGD75 paid at month 6)	SGD15 at each study assessment (baseline, month 3 and month 6)	Non-contingent payment: SGD75 Assessment payments: SGD45 Total: SGD120
Process	SGD3.50 weekly: for measuring blood glucose on 3 non-consecutive days/week SGD0.50 daily: for taking medication daily as prescribed SGD1 daily: for regular physical activity (8000 steps/day)	None	SGD15 at each study assessment (baseline, month 3 and month 6)	Maximum incentive payments: SGD336 Assessment payments: SGD45 Total: SGD45 to SGD381
Outcome	SGD2 weekly for 1 glucose reading per week being in normal range (between 4 to 7 mmol/L) SGD7 weekly for 2 glucose readings per week being in normal range (between 4 to 7 mmol/L) SGD14 weekly for 3 glucose readings per week being in normal range (between 4 to 7 mmol/L)	None	SGD15 at each study assessment (baseline, month 3 and month 6)	Maximum incentive payments: SGD336 Assessment payments: SGD45 Total: SGD45 to SGD381

SGD 1 = 0.56 GBP and USD 0.72 on 6 June 2017

#### Arm 1: Usual care (UC)

SingHealth Polyclinics have a structured framework to care for people with diabetes. Team-based care which involves the physicians, nurses, laboratory staff and pharmacists, is delivered. The model of care includes consults by the nurse clinician service and telecare service for patients with good glycaemic control; and family physician clinics, multidisciplinary teams and case managers for people with suboptimally controlled diabetes.

All new diabetes patients are referred to an in-house health counsellor for counselling and advice. The education on diabetes is done in a graded manner over four to six visits. All diabetes patients are then followed up by the physicians and nurses at 2- to 4-monthly intervals, depending on their glycaemic control. Further education by nurses is done as needed for these visits. There is an in-house laboratory at all SingHealth Polyclinics, which makes it possible to test HbA1c levels on arrival before the patient’s appointment with the physician. In addition to the follow-up consultations with polyclinic physicians, the patients are sent for annual eye and foot screening done by trained nurses. There are also in-house pharmacists who assist patients in understanding their medication doses and regimens.

In order to properly identify the effect of contingent financial incentives, we introduced slight deviations to UC. First, the participants in the UC arm will receive a Participant Leaflet (Additional files 2 and 3) reminding them of the following recommended guidelines:Participants should aim to have blood glucose levels between 4 and 7 mmol/L before mealsThe best time for participants to test their blood glucose is before breakfastParticipants should measure their blood glucose levels on at least three non-consecutive days per weekParticipants should aim to take 8000 steps every dayParticipants should take their diabetes medication(s) as recommended each day

Participants in the UC arm will also benefit from the assessment of their treatment adherence during the month-3 and monh-6 visits even though they cannot earn incentives for being adherent to the recommendations.

#### Arm 2: Process incentive

Participants in the process incentive arm will receive all the elements of UC described above and, in addition, will have the opportunity to earn financial incentives contingent on meeting specified process goals as stated below. These are also stated in the Participant Leaflet given to participants in the process incentive arm (Additional files 4 and 5):
*SGD3.50 weekly for blood glucose testing*: measuring blood glucose on three non-consecutive days each week. This will be assessed via timestamps logged by the glucometer. For the Process Incentive arm, testing counts towards the goal even when readings fall outside the recommended range. The incentive amount approximately offsets the cost of the required glucometer strips and lancets
*SGD0.50 daily for medication adherence*: taking all medications as prescribed during the day, which will be monitored by the medication tracker. This will be assessed based on medication-taking times within specified time windows. For instance, if a participant’s specified timing is 5 a.m. to 11 a.m. (breakfast) and 5 p.m. to 11 p.m. (dinner), a reading has to be logged within both windows for the participant to be considered adherent on that day. For the sake of simplicity, the incentive amount was set at the same level as for glucose testing
*SGD1.00 daily for regular physical activity*: taking 8000 steps during the day as recorded by the pedometer. The incentive amount is the double of that for glucose testing and medication adherence to account for the relative difficulty of the goal to achieve

Overall, participants can receive incentives worth up to SGD14 a week amounting to SGD336 over two 3-month (12 weeks) periods.

#### Arm 3: Outcome incentive

Participants in the outcome incentive arm will receive all the elements of UC described above and, in addition, will have the opportunity to earn financial incentives contingent on meeting health outcomes goals. Specifically, these participants will earn financial incentives for recording glucose readings within the normal range (between 4 to 7 mmol/L) before a meal on three non-consecutive days within the week as stated below. These are also stated in the Participant Leaflet given to participants in the outcome incentive arm (Additional files 6 and 7).SGD2 weekly if one glucose reading falls within the normal rangeSGD7 weekly if two glucose readings fall within the normal rangeSGD14 weekly if three glucose readings fall within the normal range

If a participant tests more than once during a day, only the first measurement will count. If a participant tests on a consecutive day, this day will not count towards the goal. Overall participants can receive incentives worth up to SGD14 a week amounting to SGD336 over two 3-month (12 weeks) periods. Note that the incentive amount was set at the same level as for the process incentive arm so that to control for incentive size.

### Outcome measures

#### Primary outcome

The primary outcome is *mean change from baseline in glycated haemoglobin HbA1c at month 6*. HbA1c is an intermediary diabetes outcome that is commonly used in the assessment of diabetes management interventions [11] and that has been shown to be strongly associated with diabetes-related complications and mortality [20].

#### Secondary outcomes

*Mean number of blood glucose days at month 6*. Up to three non-consecutive testing days during the last week of the intervention will be counted. This outcome corresponds to UC’s recommendations and to one of the goals that is incentivised in the process incentive arm
*Mean number of glucose readings that fall between 4 and 7 mmol/L at month 6*. This outcome is consistent with UC’s recommendations for blood glucose testing before meals. Consistent with the outcome incentive arm’s goal, only the first reading recorded on a maximum of three non-consecutive days will be taken into consideration during the last week of the intervention
*Mean number of medication-adherent days at month 6*. Medication-adherent days are defined as days where all medication doses were taken during pre-defined time windows as verified by the medication tracker. The number of medication-adherent days during the last week of the intervention will be calculated for each participant. This outcome corresponds to UC’s recommendation and to one of the goals that is incentivised in the process incentive arm
*Mean number of physically active days at month 6*. The number of days where the pedometer records at least 8000 steps during the last week of the intervention will be calculated for each participant. This outcome corresponds to UC’s recommendations and to one of the goals that is incentivised in the incentives arm.
*Mean cost of financial incentives at month 6.* This outcome will be calculated as the total contingent financial incentives earned by process incentive and outcome incentive arm participants during the last week of the intervention. This outcome will be used as part of the cost-effectiveness analysis
*Mean time taken by the intervention at month 6.* This outcome will be calculated as the total number of minutes spent by the CRC on adherence calculation and payment of financial incentives for process incentive and outcome incentive arms participants during the month-6 assessment. This outcome will be used as part of the cost-effectiveness analysis

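### Secondary objectives 1 and 2 ask about adherence over the whole intervention, but the listed outcomes and regressions use only its last week, and replace mean daily steps with days at or above 8000 steps

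*Protocol article*

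**What the plan says.** **Objectives.** Secondary objective 1 compares incentives with usual care on "the proportion of glucose tests and medications taken as prescribed and average number of daily steps taken between baseline and 6 months". Secondary objective 2 compares the two incentive arms on the same quantities, including "average number of daily steps between taken baseline and 6 months".

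**Secondary outcomes.** Each outcome that bears on adherence is confined to the final week:

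- Glucose testing: "Up to three non-consecutive testing days during the last week of the intervention will be counted".
- In-range readings: "a maximum of three non-consecutive days will be taken into consideration during the last week of the intervention".
- Medication: "The number of medication-adherent days during the last week of the intervention will be calculated for each participant".
- Physical activity: days with "at least 8000 steps during the last week of the intervention".

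**Secondary analyses.** These four month-6 counts are regressed linearly on the arm indicators and the baseline covariates. Neither this section nor Explanatory analyses lists a regression of adherence over the whole intervention.

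**Data available.** Under Participant timeline and study arms, all three arms receive the pedometer and medication tracker and use a glucometer. Under Data collection, glucometers and trackers are read at months 3 and 6, pedometers synchronise throughout, and the trial application calculates adherence from these data.

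**The concern.** The objectives and the outcomes describe different estimands. One is adherence averaged over the intervention. The other is adherence at its end. The two agree only if the difference between arms is constant over time, and incentive effects may well fade or build up.

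If the plan is followed as written, the report will answer a question about the final week under objectives that ask about six months. The adherence history of the whole period will not enter the comparison between arms. A participant's value will also rest on one week, which may be unusual for that person: the Data collection section itself expects overseas trips, fasting and hospital stays.

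**Working it through.** **1. Length of the intervention.** Inputs are from Table 1 and the Arm 2 and Arm 3 descriptions.

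- Process arm, weekly maximum: 3.50 + 7 × 0.50 + 7 × 1.00 = SGD14. The outcome arm's weekly maximum is also SGD14.
- Stated maximum: SGD336. 336 / 14 = 24 weeks, which agrees with the stated two periods of 12 weeks.

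The plan's own figure is reproduced.

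**2. Share of the period used.**

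- Outcome window: 1 week, so 24 − 1 = 23 weeks lie outside it (23/24 = 95.8%).
- In days: 7 of 7 × 24 = 168, or 4.2%.

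**3. Objective against outcome.**

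| Component | Objectives 1 and 2 | Outcome analysed | Difference |
|---|---|---|---|
| Glucose testing | Proportion, baseline to 6 months | Days in last week, 0 to 3 | Period; the count is a proportion times 3 |
| Medication | Proportion, baseline to 6 months | Adherent days in last week, 0 to 7 | Period; the count is a proportion of days times 7 |
| Activity | Mean daily steps, baseline to 6 months | Days at or above 8000 steps in last week, 0 to 7 | Period and measure |
| In-range readings | Not named | Readings in last week, 0 to 3 | None to reconcile |

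**4. Could the objectives mean change from baseline?** This does not fit. The pedometer and tracker are issued on joining, about half of participants are expected to have no glucometer beforehand, and no device-based measure before baseline is planned.

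**5. Can the two windows disagree?** A hypothetical example, not from the document: one arm falls linearly from 6 to 4 adherent days a week over 24 weeks, and the other stays at 5.

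- Whole-period means: (6 + 4)/2 = 5.0 against 5.0, a difference of 0.
- Last week: 4.0 against 5.0, a difference of 1 day.

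**6. Precision, for illustration only.** Assume the same correlation ICC between any two weeks. This is not given in the document.

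Variance of a 24-week mean relative to one week = ICC + (1 − ICC)/24.

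| Assumed ICC | Variance ratio | SE ratio |
|---|---|---|
| 0.4 | 0.4 + 0.6/24 = 0.425 | 0.65 |
| 0.6 | 0.6 + 0.4/24 = 0.617 | 0.79 |
| 0.8 | 0.8 + 0.2/24 = 0.808 | 0.90 |

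**The case against.** **The objectives may be the outlier.** The abstract, the Secondary outcomes and the Secondary analyses all agree on month 6. Adherence at the end of the intervention is a legitimate target and sits naturally beside month-6 HbA1c. This stands: the last-week counts are not wrong in themselves, and rewording the objectives would also remove the contradiction.

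**Four stronger readings that a reader might infer are not supported:**

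- *Adherence over the period is not measured.* It is measured in every arm, used for payments at months 3 and 6 where they apply, recorded on the visit checklists, and reviewed in the interim analyses. The gap is that no listed between-arm comparison uses the whole period.
- *The final week is untypical because a visit and payment follow.* The document gives no evidence of this. Contingent rewards accrue on the same terms every week, and all arms attend the month-6 visit. A differential rebound is possible but speculative.
- *Every measure differs from the objectives.* For testing and medication, the weekly count is largely a rescaled proportion, so the defect there is the period. One nuance remains: a day with all doses taken is not the same as a proportion of doses. Only steps clearly change measure, and the 8000 cut has a stated rationale, since it matches the usual-care advice and the incentivised goal.
- *A known amount of precision is lost.* The figures rest on an assumed ICC, ignore covariate adjustment and missing device weeks, and compare standard errors for two different estimands. They do not rank the two outcomes.

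**Conclusion.** The mismatch is explicit within the article and is not resolved elsewhere in it. Secondary objectives 1 and 2 as written have no matching analysis. The period differs for testing, medication and steps; for steps the measure differs as well. The listed comparisons use 1 of 24 weeks, although the data for the other 23 are already collected in all arms.

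This conclusion rests only on the document's text and on the 24-week length derived from its own incentive figures. It does not depend on any assumed correlation. The standard error ratio of about 0.65 to 0.90 is an illustration for an assumed ICC of 0.4 to 0.8 and carries no weight in the conclusion.

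The point concerns secondary outcomes. It should be corrected, but the primary HbA1c analysis is unaffected.

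**What to change.** **Preferred.** Add three outcomes over the full 24 weeks and name them as the analysis of secondary objectives 1 and 2:

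- proportion of required testing days completed;
- proportion of medication-adherent days;
- mean daily steps.

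Use the regression already specified in Secondary analyses. Keep the last-week counts, labelled as end-of-intervention outcomes. A whole-period version of in-range readings is optional, because neither objective names them.

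**Minimum.** Reword objectives 1 and 2 to match the last-week counts, including days at or above 8000 steps. This removes the contradiction but leaves 23 weeks of data out of the comparison.

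**Cost.** No new data collection is needed, since the trial application already processes the device data. The work is wording, data processing and an amendment notified to the ethics board. There is a small downside. The trial is open-label, 140 of 240 participants were enrolled by 31 May 2017, and interim looks at adherence are planned at 80 and 160 completers. The amendment should therefore be dated and state whether anyone involved in the decision had seen adherence data by arm.
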